### Procedures for selecting participants and randomization

Eligible patients will be invited to participate and those who agree will be included in the study and then will be allocated to either a protocol of not conducting an episiotomy or a protocol of selective episiotomy, according to a random list of numbers generated by the Random Allocation Software Ispharan Iran, version 1.0. This list of randomization will be provided by the statistician to researcher who will be responsible for preparing the envelopes containing instructions regarding which group the patient is allocated to (A: Intervention= > not to use episiotomy or B: Control= > selective episiotomy). This procedure will be followed in order to guarantee the concealment of allocation of patients in both arms. Patients and medical staff will not be blind to the intervention condition, but the researcher and the statistician performing the analysis will be blinded to the meaning of the letters A or B to which participants will be allocated.

During the observation period the birth attendants will conduct delivery of baby and placenta according to routine practice, except for the instruction about the use of episiotomy. Birth attendants will collect, using special plastic bags, blood loss after delivery and the amount will be registered. Blood from the cord will be collected to perform pH analysis, and suture of any lacerations that may occur will be performed according to their clinical judgment. After 24 hours of delivery, women will be interviewed and perineal pain will be evaluated using a visual pain scale and women’s satisfaction will also be assessed. During the observation period, if before birth occurs, there is an indication of cesarean delivery, the women will be excluded from the study.

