### Eligibility criteria

Laboring women with term pregnancy, maximum dilation of 8 cm, live fetus in cephalic vertex presentation will be included and women with bleeding disorders of pregnancy, immediate indication for caesarean section and women without capacity to consent and without legal guardians will be excluded.

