### Sample size calculation

The sample size was calculated on the Open Epi 2.3 (Atlanta, GA), with an expected rate of episiotomies in the protocol group of not conducting episiotomy of 1% versus a 10% rate of episiotomies in the group of episiotomy selective [3,4]. For a power of 80% and a confidence level of 95%, 200 women would be needed, a figure that has increased by 20% to compensate for eventual losses after randomization, so that 240 women will be randomized.

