### Data analysis plan

The data analysis will be performed using the public domain software Epi Info version 7.1.4 (Centers for Disease Control and Prevention, Atlanta, GA), or the newest available version under the intention to treat principle. The statistician will remain blind to the meaning of the Groups A or B to which patients are allocated until the tables and the analysis concluded. The approach for analysis will be that showed in Figure 1 using an intention-to-treat strategy and following the correspondent recommendations from the CONSORT statement [11]. The characteristics of the participants in each group will be compared with Student’s *t* test for continuous variables with normal distribution and Mann–Whitney U test for discrete and ordinal variables or those with non-normal distribution. Categorical variables will be compared with Pearson’s χ [2] test or Fisher’s exact test, as appropriate. P values for all tests will be two tailed at a 5% level of significance. Risk ratios and their 95% confidence intervals will be calculated as a measure of relative risk. The number needed to treat (NNT) and its 95% confidence interval will be calculated for the outcomes in which a beneficial effect of not performing an episiotomy is achieved, using the EBM calculator [http://moosenose.com/EBCalculator.htm]; in case of adverse effects the number needed to harm (NNH) and its 95% confidence will also be calculated.

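### The planned tests are valid but crude; a prespecified analysis by previous vaginal birth would recover precision on second-stage and perineal outcomes if parity is prognostic

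*Protocol article*

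**What the plan says.** Three sections of the protocol article bear on this.

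- **Eligibility criteria:** "Laboring women with term pregnancy, maximum dilation of 8 cm, live fetus in cephalic vertex presentation will be included". Parity is not mentioned, so first-time mothers and women with earlier vaginal births enter together.
- **Procedures for selecting participants and randomization:** women are allocated "according to a random list of numbers generated by the Random Allocation Software Ispharan Iran, version 1.0". The list is then spoken of in the singular: "This list of randomization will be provided by the statistician to researcher who will be responsible for preparing the envelopes". No strata, blocks or minimisation factors are named.
- **Data analysis plan:** Student's t or Mann-Whitney tests for continuous and ordinal variables. For the rest, "Categorical variables will be compared with Pearson’s χ [2] test or Fisher’s exact test, as appropriate". Risk ratios with 95% confidence intervals are the effect measure, and "P values for all tests will be two tailed at a 5% level of significance". No covariate or stratified method is named. The sentence on the t and Mann-Whitney tests speaks of participants' characteristics. I read it as covering outcomes too, since no other test is given.

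**The concern.** Whether a woman has given birth vaginally before can be recorded before her envelope is opened. It is a plausible predictor of second-stage duration, lacerations, suturing and instrumental delivery. An analysis that ignores such a predictor leaves its share of the variance in the error term, and it has no means of correcting for a chance difference in parity between the arms.

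This matters most for outcomes that the Main hypothesis section expects to be the same in both arms, namely second-stage duration, spontaneous lacerations and perineal trauma. The sample was sized on the episiotomy rate alone, so precision on these other outcomes is whatever about 100 women per arm happens to give. A chance parity gap could then make one result look like harm or like reassurance.

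**Working it through.** **1. The plan's own figure.** Inputs from Sample size calculation: "expected rate of episiotomies in the protocol group of not conducting episiotomy of 1% versus a 10% rate of episiotomies"; "For a power of 80% and a confidence level of 95%, 200 women would be needed". With the pooled-variance formula, 1:1 allocation (assumed, as the ratio is not stated) and no continuity correction, the mean proportion is 0.055 and

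n per arm = [1.96·√(2·0.055·0.945) + 0.842·√(0.10·0.90 + 0.01·0.99)]² / 0.09² = 99.5, so 100 per arm and 200 in total.

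The stated figure reproduces, and 200 × 1.20 = 240 as stated ("increased by 20% to compensate for eventual losses after randomization, so that 240 women will be randomized"). Nothing below changes it. I use 100 per arm as the number analysed, and 120 as the number per arm if nobody is lost.

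**2. Chance of a parity gap.** The share q of women with no previous vaginal birth is not given, so I assume 30% to 60%. The SD of the between-arm difference in that share is √(2q(1−q)/n).

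| q | SD, n = 100 | Chance of gap ≥ 10 points, n = 100 | Chance of gap ≥ 10 points, n = 120 |
|---|---|---|---|
| 0.3 | 6.5 points | 12.3% | 9.1% |
| 0.5 | 7.1 points | 15.7% | 12.1% |
| 0.6 | 6.9 points | 14.9% | 11.4% |

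**3. What such a gap does.** Let d be the parity effect in within-group SDs (assumed). A 10-point gap shifts the arm difference by 0.10·d, which is 0.05 SD at d = 0.5 and 0.10 SD at d = 1.0. The standard error at 100 per arm is √(2/100) = 0.14 SD, so the shift is about 0.35 to 0.7 standard errors. Given a 10-point gap and q = 0.5, the type I error of the crude test is 5.7% (d = 0.5) or 7.1% (d = 1.0). Given a 14-point gap, roughly the edge of the 95% range, it is 7.0% or 11.6%. Averaged over all randomisations it stays at 5%: 20,000 simulated trials each gave 5.1% and 5.3%.

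**4. Precision lost by not adjusting, continuous outcome.** R² = q(1−q)d² / (1 + q(1−q)d²), and the crude comparison needs 1/(1−R²) = 1 + q(1−q)d² times as many women. With q = 0.5:

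| d | R² | Extra women needed |
|---|---|---|
| 0.3 | 0.022 | 2% |
| 0.5 | 0.059 | 6% |
| 0.8 | 0.138 | 16% |
| 1.0 | 0.200 | 25% |

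At q = 0.3 the factor q(1−q) falls from 0.25 to 0.21, so the top figure becomes 21%. The formula is for means; for a rank test it is only a guide.

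**5. The outcome that sized the trial.** If the 10% control rate is made up of 15% and 5% in two equal parity groups (assumed), R² = 0.25·0.10² / (0.10·0.90) = 0.028, about 3%. A 10-point gap moves the control rate by 0.10 × 0.10 = 1 point. Even a split of 18% and 2% gives only 0.25·0.16² / 0.09 = 7%. In the other arm, at 1%, the most extreme equal-group split (2% and 0%) gives 0.25·0.02² / (0.01·0.99) = 1%.

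**The case against.** The strongest reply is that nothing here is an error. Simple randomisation is a valid design, the crude tests hold their level, and their confidence intervals already allow for chance imbalance. That stands in full. A reader might infer that a single unstratified list biases the trial. It does not: the conditional error rates in step 3 are part of ordinary sampling error, and they average out to 5%.

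Second, the article never says that the list is unstratified; that is read from its silence, and a fuller protocol or SAP may hold a stratification factor or covariate. This also stands, and it is why the point is a proposal about the analysis that the article describes, not a charge of omission.

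Third, the article does not mention parity and gives no effect of it. A reader might infer that first-time mothers differ strongly on almost every primary outcome. The document supports no such statement, and nothing is shown for Apgar scores, resuscitation, cord pH or blood loss. A reader might also expect a much larger gain. A 40-minute parity difference against a 25-minute SD, for example, is 1.6 SD and gives 1 + 0.25·1.6² = 1.64, or 64% more women. That depends on an effect for which the document offers no basis.

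Finally, it is tempting to blame the list. Stratifying it while keeping crude tests would not recover the precision, whereas adjusting would, even with an unstratified list. Women who develop an indication for caesarean before birth are excluded after randomisation, so a stratified list would not guarantee balance among those analysed either.

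**Conclusion.** A minor, worthwhile improvement to the Data analysis plan; not a mistake or a contradiction. On the assumptions shown (parity effect of 0.3 to 1.0 within-group SD, even split, 100 per arm), adjusting a continuous outcome such as second-stage duration is worth about 2% to 25% more women. It is worth about 3% for the episiotomy rate, so the primary sample size argument is barely touched. It would also remove the shift of 0.05 to 0.10 SD that a 10-point parity gap brings at effects of 0.5 to 1.0 SD. If parity turns out not to be prognostic, there is almost nothing to gain and almost nothing to lose.

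**What to change.** In the Data analysis plan, before unblinding (while the group letters are still undecoded), prespecify analysis by previous vaginal birth, none versus at least one, recorded before allocation:

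- **Lacerations, perineal trauma, need for suturing, instrumental delivery and episiotomy:** Mantel-Haenszel risk ratios and risk differences with 95% confidence intervals. The risk difference is useful for episiotomy because only about one event (100 × 1%) is expected in the no-episiotomy arm.
- **Second-stage duration and number of sutures:** a parity-adjusted model or, where a rank test is preferred, the van Elteren test.
- **Crude results:** report them alongside.

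If enrolment has not begun, the list may also be stratified by the same factor, with one envelope series per stratum. This is an optional addition; most of the benefit comes from the analysis.

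The cost is slightly more analysis work and, if the list is stratified, a small risk that staff take an envelope from the wrong series. No extra women or procedures are needed.

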### Data collection procedures

#### ***Data collection***

For data collection, a pre-coded standard form will be used for data entry on the computer. After identifying the patients who are according to the eligibility criteria, using a specific check list, and who agree to participate in the study and sign the informed consent form, information will be collected and filled in the form. The checklist, as well as the form will be completed by the researchers.

Upon completion, the forms will be rigorously reviewed by the researchers to cross-check the information collected with the information contained in the records. Procedures for quality control, such as reviewing the completed forms and check manually typing will be adopted. A first quality control of data collection should be done before and during the typing of electronic records, to identify possible inconsistencies in the data researcher. The second quality control will check the compatibility between the physical archived records and data contained in electronic forms. The data will be entered in a specific database, created using the Epi Info statistical program 7.1.4. Each month the database will be reviewed by the principal investigator, getting listing of variables and correcting any inconsistencies or missing information from the query to the forms.

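### Allocation concealment is not secured by the procedure described: a researcher holds the decoded list, the researchers screen, and nothing in the text separates the two roles

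*Protocol article*

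**What the plan says.** Three statements in Procedures for selecting participants and randomization bear on this point.

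- On the list: "This list of randomization will be provided by the statistician to researcher who will be responsible for preparing the envelopes". The envelopes are described as "containing instructions regarding which group the patient is allocated to (A: Intervention= > not to use episiotomy or B: Control= > selective episiotomy", so whoever prepares them works with both the sequence and its meaning.
- On the purpose: "This procedure will be followed in order to guarantee the concealment of allocation of patients in both arms".
- On blinding, after stating that patients and staff are not blind: "the researcher and the statistician performing the analysis will be blinded to the meaning of the letters A or B".

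The same section gives the order of entry without naming who acts: "Eligible patients will be invited to participate and those who agree will be included in the study and then will be allocated".

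Data collection says who screens. The checklist is the tool for finding eligible women ("After identifying the patients who are according to the eligibility criteria, using a specific check list, and who agree to participate in the study"), and "The checklist, as well as the form will be completed by the researchers".

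**The concern.** Concealment means that whoever decides whether, and when, a woman enters the trial cannot know the next assignment. The article presents its envelope procedure as a guarantee of this. Yet the step it describes places the whole decoded sequence with a member of the research team, and the research team does the screening. This is a stated step, not a detail that a condensed article has merely left out.

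Several features make the point more than formal. The trial is open label (Study design), and a directional hypothesis favours never performing episiotomy (Objectives and hypothesis). Entry involves some judgement and timing: dilation may be anything up to 8 cm, and the caesarean exclusion turns on whether the indication is immediate (Eligibility criteria). If someone who knew the next assignment also had a say in entry, the arms could differ in risk before treatment began. Intention-to-treat analysis does not correct such a difference.

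This is separate from masking the letters A and B at analysis. That masking protects the analysis. It does nothing to stop a list holder from knowing the next allocation.

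**Working it through.** The point is procedural, so the main check sets the statements side by side.

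1. **Who knows the sequence?** The statistician who supplies the list, and the researcher who receives it and prepares the envelopes. The envelopes name the arm, so the preparer also knows what each letter means.
2. **Who screens?** The researchers, in the plural, complete the eligibility checklist.
3. **Who invites, enrols and opens the envelope?** Not stated. Invitation and allocation are in the passive voice.
4. **Is the person in step 1 kept out of step 2 or 3?** No sentence says so, and no sentence says the opposite.
5. **Does the procedure support the word guarantee?** It would if step 4 were answered by a stated separation of roles. Without one, concealment depends on an arrangement that the text does not describe.
6. **Is the blinding sentence consistent?** Whoever prepares envelopes that define A and B cannot be blind to those letters. Two readings are open. In the first, the same researcher is meant, and the section contradicts itself. In the second, the words about performing the analysis apply to the researcher too, so a different person is meant. The text does not say which.

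**Figures.** The plan gives no figure for this point. Its sample size is not affected. From an "expected rate of episiotomies in the protocol group of not conducting episiotomy of 1% versus a 10% rate of episiotomies", with two-sided 5%, 80% power, an assumed 1:1 ratio and no continuity correction:

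n per arm = [1.96 × √(2 × 0.055 × 0.945) + 0.842 × √(0.01 × 0.99 + 0.10 × 0.90)]² / 0.09² ≈ 99.5, rounded up to 100.

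That is 200 in total, and 200 × 1.2 = 240, as stated. With 1:1 allocation, 240 means 120 per arm.

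**Illustration of scale, with all inputs assumed.** Suppose 12 higher-risk women move from A to B in exchange for 12 lower-risk women, and some outcome differs by d points between the two kinds of women. Each arm shifts by (12/120) × d, in opposite directions, so the spurious difference is 2 × (12/120) × d = 0.2 × d.

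| d (points) | shift per arm (points) | spurious difference (points) |
|---|---|---|
| 15 | 1.5 | 3 |
| 30 | 3 | 6 |
| 40 | 4 | 8 |

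The share steered, its direction and d are all assumptions. The table shows what foreknowledge could do if it were used, not what is expected in this trial.

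**The case against.** The strongest reply is that the link between list holder and recruiter is inferred. One researcher prepares envelopes, and the researchers complete the checklist. Nothing says that the first is among the second, and no actor is named for invitation or enrolment. A team member who makes envelopes from a list breaches nothing if that person stays out of recruitment. This stands. A reader might infer that recruiters will know upcoming allocations, or that concealment is broken. The article supports neither; it shows only that concealment is not secured by what is described.

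Three further replies also hold in part:

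- A journal article condenses a full protocol that is not shown. Envelope format (opaque, sealed, numbered) is commonly left to that document, so its absence carries no weight here. The point rests on the stated handover and the stated guarantee.
- Agreement before allocation is already the stated order, so no change is needed there.
- A reader might go on to infer that every outcome would be biased beyond repair. That would need a list holder who recruits, who steers, and who does so on predictors of each outcome. None of this is in the documents. The Data analysis plan also compares participant characteristics between arms, so imbalance in recorded factors could be seen and partly adjusted for. Unrecorded factors would remain.

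The blinding sentence could be taken as a sign that roles are divided. If so, the division should be stated, because the other available reading is a contradiction.

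**Conclusion.** The point holds in a limited form. The article gives the sequence and its meaning to a researcher, has the researchers screen, states no separation between them, and claims a guarantee that these steps do not deliver. The blinding statement conflicts with the envelope step unless it refers to someone else.

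The size of any bias cannot be derived from the documents. The range of 3 to 8 points rests wholly on assumed inputs. It should not be set against the difference in episiotomy rates used for the sample size, because the illustration concerns some other outcome, such as suturing. The conclusion assumes that the article's wording reflects the procedure to be used. If the full protocol already separates the roles, only the article's wording needs correcting. The change is worth making because selection at entry is hard to detect or repair afterwards, and the remedy is cheap beforehand.

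**What to change.** In Procedures for selecting participants and randomization, replace the handover to a researcher with a statement that the list is held, and the envelopes prepared, by someone in the statistician's office or another existing person who has no role in screening, consent, enrolment or data collection. If the statistician's office is chosen, it should be someone other than the statistician who performs the analysis, because preparing the envelopes would reveal what A and B mean. In the same section, state which researcher is blind to A and B, so that the blinding sentence no longer conflicts with the envelope step.

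The cost is a sentence or two of text and the one-off preparation of 240 envelopes by a person outside recruitment. The small downside is that the recruiting team gives up that task. Sample size, outcomes and analysis are unchanged.

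### Women in whom a caesarean indication arises after randomisation are excluded from the study, which contradicts the stated intention-to-treat analysis and lets knowledge of the arm influence who is analysed

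*Protocol article*

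**What the plan says.** The order of events is in the Protocol article, Procedures for selecting participants and randomization. Women are recruited first: "those who agree will be included in the study and then will be allocated to either a protocol of not conducting an episiotomy" or to selective episiotomy. Later in the same section, for the observation period, the rule is that "if before birth occurs, there is an indication of cesarean delivery, the women will be excluded from the study". The section also says "Patients and medical staff will not be blind to the intervention condition".

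This is not the entry criterion. Under Eligibility criteria, women with an "immediate indication for caesarean section" are kept out before allocation. Entry is open to "Laboring women with term pregnancy, maximum dilation of 8 cm", so an indication can still arise between allocation and birth.

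The Data analysis plan names intention to treat twice, the second time as "using an intention-to-treat strategy and following the correspondent recommendations from the CONSORT statement". Nothing in the article says that the excluded women stay in the analysis, defines a modified intention-to-treat set, or provides for a blinded or independent judgement of the caesarean indication. Caesarean delivery is absent from the lists of primary and secondary outcomes and from the dependent variables.

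**The concern.** An intention-to-treat comparison keeps each randomised woman in her allocated arm. Removing some of them for an event after allocation gives up the balance that randomisation provides, unless the event is unaffected by the arm. That cannot be assumed here. The trigger is an indication, which is a clinical judgement, and it is made at the bedside by unblinded staff. Blinding the statistician to the group letters does not help, because the selection has happened before the data reach the analysis.

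The neonatal outcomes are the most exposed. The Main hypothesis expects Apgar scores, resuscitation and cord pH to be the same in both arms, and neonatal morbidity and NICU admission to be similar. If difficult births left one arm more often than the other, that expectation could be met or missed because of who was removed. Women are excluded from the study, not just from one analysis. If their data are not collected, no later analysis plan can restore the comparison.

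**Working it through.** **1. The plan's own sample size.** Inputs from Sample size calculation: episiotomy rates "of 1% versus a 10% rate of episiotomies in the group of episiotomy selective"; "For a power of 80% and a confidence level of 95%, 200 women would be needed". The test is two-sided at 5% (Data analysis plan).

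n per arm = [1.960·√(2·p̄·q̄) + 0.842·√(p₁q₁ + p₂q₂)]² / (p₂ − p₁)², with p₁ = 0.01, p₂ = 0.10, p̄ = 0.055 and q = 1 − p.

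= [1.960·√0.10395 + 0.842·√0.0999]² / 0.09² = 0.806 / 0.0081 = 99.5, so 100 per arm and 200 in total. The stated figure is reproduced. The 20% increase gives 200 × 1.2 = 240.

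**2. Numbers lost.** If a share c is excluded, 240 × (1 − c) women remain. This stays at 200 or more while c ≤ 40/240 = 16.7%.

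**3. Power for episiotomy frequency.** The article gives no caesarean rate, so c is an assumption, equal in both arms, with no episiotomy in women delivered by caesarean. Keeping them gives rates of 0.01(1 − c) and 0.10(1 − c) in 120 per arm. Dropping them gives 0.01 and 0.10 in 120(1 − c) per arm.

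| Assumed c | Power, all 240 kept | Women left if dropped | Power, dropped |
|---|---|---|---|
| 5% | 85.0% | 228 | 85.1% |
| 10% | 82.9% | 216 | 83.1% |
| 15% | 80.5% | 204 | 81.0% |
| 20% | 78.0% | 192 | 78.5% |
| 30% | 72.0% | 168 | 72.9% |

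The largest difference is 0.9 points. The risk ratio is 0.1 either way. At c = 15%, the absolute difference is diluted from 9 points to 8.5% − 0.85% = 7.65 points.

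**4. Selection in a neonatal outcome (illustration only).** All inputs are assumptions:
- 15% of control women are removed for caesarean.
- A further share e is removed only if allocated to no episiotomy.
- Low cord pH occurs in 30% of those extra women and in 6% of the remaining analysed women.
- Allocation has no true effect on cord pH.

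In control, the women making up e are still analysed: rate = [0.30e + 0.06(0.85 − e)] / 0.85. In the no-episiotomy arm they are gone: rate = 6.0%.

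| Extra removed, e | Control rate | No-episiotomy rate | Spurious RR |
|---|---|---|---|
| 1 point | 6.28% | 6.0% | 0.96 |
| 2 points | 6.56% | 6.0% | 0.91 |
| 3 points | 6.85% | 6.0% | 0.88 |
| 5 points | 7.41% | 6.0% | 0.81 |

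If the extra removals fell in the selective arm instead, the ratios would invert: 6.28/6.0 = 1.05 for 1 point and 7.41/6.0 = 1.24 for 5 points.

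**5. A ceiling on e.** Suppose the only route is that a withheld episiotomy becomes a caesarean. Then e cannot exceed the episiotomies averted. With 15% caesarean and the planning rates applied to vaginal births, that is 0.85 × (10% − 1%) = 7.65 points. Five points would already mean 5/7.65, about 65%, of the averted episiotomies ending as caesareans, so it is a high value.

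**The case against.** **The 20% allowance already covers this.** It covers how many women are lost, up to 16.7%, and to that extent the objection stands. It does not address which women are lost.

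**The sized endpoint is barely touched.** This stands. A reader might infer that the exclusions threaten the power of the trial. The table shows that keeping or dropping these women makes almost no difference.

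**The mechanism is inferred.** A reader might conclude that caesarean decisions rest on the same problems for which the control arm may use episiotomy, so that difficult births will leave the no-episiotomy arm. The article lists prolonged second stage, non-reassuring fetal heart rate and instrumental delivery as reasons for episiotomy. It lists no caesarean indications, so the overlap is a clinical inference. The no-episiotomy arm also keeps a force majeure exception, which weakens the route. The text shows that the arm can influence exclusion, not that it will.

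**A shift would show in the participant flow.** A reader might infer that a difference in caesareans would go unseen. Caesarean is not a listed outcome, but the analysis is to follow CONSORT and Figure 1, which is not available here and may show exclusions by arm. Even so, a count of exclusions does not recover outcomes that were not collected.

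**Some outcomes have no meaning after caesarean.** This stands. Under Main outcomes, second-stage duration starts at full dilation with pushing, so it is undefined for a caesarean before that point. Counting every caesarean as no perineal trauma in the main analysis is not neutral either. If 40% of vaginal births have trauma (the Introduction cites an uncontrolled study with about 60% intact) and caesarean is 20% against 15%, the rates become 0.80 × 40% = 32% against 0.85 × 40% = 34%, a ratio of 0.94 with no true effect. This limits the remedy for those outcomes. It does not justify removing the women from the study.

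**Conclusion.** The contradiction is in the current text and needs no assumption: a rule that excludes randomised women for a judgement made after allocation cannot stand beside an intention-to-treat analysis. It must be fixed, because following the plan as written can bias the comparison, chiefly for the neonatal outcomes.

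The size and direction of that bias are unknown. The range of 0.96 to 0.81 depends wholly on the assumed caesarean rate, excess removals and cord pH risks. A reader should not take it as an estimate, nor infer that the no-episiotomy arm will look falsely safe, since the documents supply none of these inputs and the bias could run the other way.

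**What to change.** Reconcile Procedures for selecting participants and randomization with the Data analysis plan:

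- Replace the exclusion sentence with a statement that all randomised women are followed and analysed in their allocated arm.
- List caesarean delivery as an outcome, reported by arm.
- Analyse episiotomy frequency, Apgar scores, resuscitation, cord pH, neonatal morbidity, NICU admission and satisfaction in all randomised women.
- For outcomes not defined or not comparable after caesarean (second-stage duration, lacerations, suturing, instrumental delivery, blood loss at vaginal birth), report the vaginal-birth analysis, labelled as conditioned on a post-randomisation event, with caesarean rates by arm beside it.
- For the perineal outcomes, add a sensitivity analysis in all randomised women that counts caesarean as no perineal event.

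The cost is a wording change, completing the existing form for women delivered by caesarean, and a slight dilution of the episiotomy contrast. The change concerns who is followed and analysed, and leaves clinical care as it is.
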